**Methods and analysis:**

This multicentre, assessor-blinded, randomised controlled trial will recruit 98 Chinese-speaking inpatients following ACS with evaluation at 1 and 3 months postdischarge. Control participants in the control group will receive the usual ward-based patient discharge education. Intervention participants will additionally receive the education app installed on their devices before hospital discharge with unlimited access during the study period. Cultural relevance and linguistic accuracy for this Chinese version of an existing app were ensured through co-adaptation with Chinese-speaking consumers; the primary outcome will be coronary heart disease (CHD) knowledge, and secondary outcomes will include knowledge, attitudes and beliefs regarding heart attack symptoms and responses, CHD self-management behaviours, utilisation of healthcare services and quality of life. A process evaluation will be conducted alongside the trial to assess the acceptability and feasibility of the app. Between-group comparisons will be made using 95% CIs, accounting for baseline differences using linear mixed effects or mixed effects logistic regression models.

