## Methods and analysis

### Study design

This study is a prospective, outcome assessor-blinded, multicentre, randomised controlled trial (RCT) of a discharge education app for Chinese-speaking patients with ACS that uses a virtual avatar nurse to guide users (figure 1). The trial will compare this app plus usual care with usual care alone in Chinese-speaking patients with ACS. A process evaluation will be conducted following the RCT. This study protocol was developed following the Standard Protocol Items: Recommendations for Interventional Trials Checklist.^28^ The trial has been prospectively registered with the Australia and New Zealand Clinical Trial Registry (ACTRN12624000408583).

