### Setting and recruitment

This study will be conducted at three large tertiary public hospitals in metropolitan Sydney, Australia, which serve large populations with diverse social, economic and cultural backgrounds. China-born residents rank among the top overseas-born groups in the catchment area of these hospitals. The care provided in these hospitals is funded by Medicare-Australia’s universal health insurance scheme.

Cardiology ward staff who are not part of the research team will screen the admission lists of the wards at the participating hospitals to identify potential participants. A bilingual researcher will approach the potential participants to explore their interest in participating. Following informed consent, patients will be enrolled in the study and complete a baseline assessment by the bilingual researcher before randomisation. The baseline assessment will include participants’ demographic (age, gender, education, English proficiency, health literacy, marriage status, employment status, technology use) and clinical data (admission diagnosis, comorbidities). Patients who are ineligible or decline to participate will be recorded, and the reason for exclusion or refusal will be documented. Recruitment is anticipated to take place between 1 July 2024 and 31 August 2026.

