**Other secondary outcomes**				
Cardiac-related mortality	Family reported		✓	✓
Quality of life	EQ-5D-5L	✓		✓
App acceptability	App user survey		✓	
App feasibility	Data analytics			✓
Barriers and facilitators of implementation	Individual interview and focus group			✓

C-ACSRI, Chinese version of Acute Coronary Syndrome Response Index; CADE-Q SV, short version of the Chinese-language Coronary Artery Disease Education Questionnaire; CADSMS, Coronary Artery Disease Self-Management behaviour Scale; CHD, coronary heart disease; EQ-5D-5L, Five-Level EuroQol five-dimension instrument.

The primary outcome will be the mean difference between intervention and control groups in CHD knowledge scores and knowledge, attitudes and beliefs about heart attack symptoms and responses. Key secondary outcomes will include CHD self-management behaviours, cardiac-related hospital admission and use of healthcare services. Other secondary outcomes will include cardiac-related mortality, quality of life, app acceptability, app feasibility and barriers and facilitators of implementation.

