#### Self-management behaviours

Participants’ CHD self-management behaviours will be measured 3 months posthospital discharge using the Coronary Artery Disease Self-Management behaviour Scale. This 27-item questionnaire has three subdomains, including emotional self-management behaviours, daily life self-management behaviours and medical self-management behaviours. Participants rate each item on a 5-point Likert scale, for a total score ranging from 27 to 135, with a higher score indicating better self-management behaviours. The questionnaire was originally developed and validated in Chinese patients with CHD.^36^

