#### Quality of life

Quality of life will be measured 3 months posthospital discharge using the Five-Level EuroQol five-dimension instrument (EQ-5D-5L) (Simplified Chinese).^37^ Participants will be assessed across five health dimensions, including mobility, self-care, usual activities, pain/discomfort and anxiety/depression, based on five response categories from level 1 to 5 corresponding with no problem, slight problems, moderate problems, severe problems and extreme problems, respectively.^38^ Alongside the five health dimensions, the EQ visual analogue scale will be used to assess participants’ ‘own health today’ with end points labelled ‘best imaginable health state’ (100) and ‘worst imaginable health state’ (0). The EQ-5D-5L has been validated in Chinese populations.^37^

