### Statistical analysis

Statistical analysis will follow the intention-to-treat principle and a prespecified statistical analysis plan led by a blinded statistician. Descriptive statistics will be used to characterise participants. The analysis of variance (ANOVA) will be used to compare the primary outcome and estimate the mean difference and 95% CI. Furthermore, to assess whether there is a change in the outcome over time (baseline, 1 month and 3 months) within and between groups, a linear mixed effects regression model will be used with a random intercept for patients to account for individual variability. Assumptions for ANOVA and the linear mixed-effects model will be assessed prior to analysis. For ANOVA, independence, normality within groups and homogeneity of variances will be checked using Levene’s test, and outliers will be addressed if necessary. For the mixed-effects model, linearity, residual normality and homoscedasticity will be evaluated through diagnostic plots. If assumptions are violated, corrective measures such as data transformation or robust methods will be applied. In the case of missing data that are missing at random in nature, multiple imputations will be used. For secondary continuous outcomes, linear mixed effects regressions will be performed to assess whether there is change in the outcomes over time within and between groups. Similarly, for secondary categorical outcomes, mixed effects logistic regression models will be used to test for the change in the outcomes over time within and between groups.

Interview audio files will be transcribed verbatim into simplified Chinese and then translated into English by a bilingual researcher. To ensure the accuracy and reliability of the translation, another bilingual author will randomly audit five translated transcripts and back-translate these from English into simplified Chinese. The data will then be analysed using directed content analysis, with coding and theme generation facilitated by an Excel spreadsheet.

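### Within-group change from an in-hospital baseline is a stated analysis target for secondary outcomes, but it cannot inform about the app; it should be descriptive, with conclusions resting on the baseline-adjusted between-group difference at 3 months

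*Protocol article*

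**What the plan says.** The Statistical analysis section describes the models for secondary outcomes in two sentences. For continuous outcomes, "linear mixed effects regressions will be performed to assess whether there is change in the outcomes over time within and between groups". For categorical outcomes, "mixed effects logistic regression models will be used to test for the change in the outcomes over time within and between groups". Both sentences put within-group and between-group change side by side. Nothing in the article says that one is descriptive and the other inferential.

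On timing, the Setting and recruitment section says that "patients will be enrolled in the study and complete a baseline assessment by the bilingual researcher before randomisation". The Intervention section places installation of the app after baseline and randomisation but before discharge. Participants are patients admitted with ACS, so the baseline score belongs to the index admission. Table 1 schedules the self-management scale and the EQ-5D-5L at baseline and 3 months only.

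Elsewhere the protocol points to the randomised comparison. The abstract states: "Between-group comparisons will be made using 95% CIs, accounting for baseline differences using linear mixed effects or mixed effects logistic regression models". Under Study design, "The trial will compare this app plus usual care with usual care alone in Chinese-speaking patients with ACS".

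**The concern.** A change from baseline within one arm has no comparator. With this baseline, it starts from the state of an inpatient with an acute coronary event; the EQ visual analogue scale asks about health on that day. By 3 months the patient has been treated, has gone home and has had usual care. A change in the app arm contains all of that plus whatever the app adds, and the within-arm analysis cannot separate the parts.

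Two results would then be easy to misreport. One is improvement in both arms presented as benefit of education. The other is a significant change in the app arm and a non-significant one in control, taken as a difference between the arms. Neither is evidence about the app.

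A second consequence concerns precision. For an outcome with two time points, a random-intercept model built around change over time, with group, time and their interaction, amounts to comparing change scores. That is less precise than using the baseline score as a covariate.

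**Working it through.** **1. Number per arm (Sample size calculation section).** Inputs: difference 2.3, SD 3.6, α = 0.05 (taken as two-sided), power 80%, dropout 20%.

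- n per group = 2 × (1.960 + 0.842)² × 3.6² / 2.3² = 2 × 7.849 × 12.96 / 5.29 = 38.5, rounded up to 39; total 78.
- 78 / (1 − 0.20) = 97.5, rounded up to 98.

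Both stated figures reproduce. Power at 39 per group is 80.5% by the normal approximation and 79.5% by the t test. The sample size is for a between-group difference in knowledge and is not affected by this point. It only supplies the 39 completers per arm used below.

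**2. Behaviour of a within-arm test when the app does nothing.** The documents give no expected recovery in quality of life or self-management, so its size is assumed and shown as a range. Let d be the true mean change in SDs of the change score, equal in both arms. A one-sample t test of change in one arm has 38 degrees of freedom, critical value 2.024 and non-centrality d × √39 = 6.245d. The between-group test is a two-sample t test on change. Results are from 50,000 simulated trials per row.

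| Assumed shared recovery d | Non-centrality | App arm significant | App arm significant, control not | Between-group test significant |
|---|---|---|---|---|
| 0.2 | 1.25 | 23% | 17% | 5.0% |
| 0.3 | 1.87 | 45% | 25% | 4.8% |
| 0.5 | 3.12 | 86% | 12% | 5.0% |
| 0.8 | 5.00 | 99.8% | 0.2% | 5.0% |

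The third column rises with recovery alone, with no app effect. The fourth does not rise steadily: with independent arms and common significance probability p it equals p(1 − p), which peaks at p = 0.5 and vanishes as p approaches 1. The last column stays at the nominal level because shared recovery cancels.

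The t test stands in for the within-arm contrast of a mixed model. The protocol does not specify separate paired tests by arm, so the table is an illustration and not a reproduction of the planned analysis.

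**3. Gain from baseline as a covariate.** Let σ² be the variance of the score, taken as equal at both times, and r the correlation between baseline and 3 months.

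- Change score: variance per patient 2σ²(1 − r).
- Covariate-adjusted 3-month score: σ²(1 − r²).
- Ratio: (1 − r²) / [2(1 − r)] = (1 + r)/2.

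At an assumed r of 0.3 the ratio is 0.65; at 0.5 it is 0.75. Since √0.65 = 0.81 and √0.75 = 0.87, confidence intervals would be about 19% or 13% narrower.

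**The case against.** The strongest reply is that the trial already has what it needs. It has a concurrent randomised control arm, both arms share the same pre-randomisation baseline, and the abstract commits to between-group comparisons that account for baseline. All of that stands. A reader might infer that the in-hospital baseline biases the estimated app effect. It does not, because shared recovery cancels in the randomised contrast.

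A reader might also infer that the protocol intends to treat within-group change as an app effect. No section says so. For continuous outcomes the verb is to assess; testing is named only for categorical ones. The misreading is a risk that the wording leaves open, not a stated plan.

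The pattern of app arm significant and control not should not be given as a fixed rate. It is 25% at 0.3 SD but 0.2% at 0.8 SD, so the stronger the recovery, the rarer it is. It is also a pattern of p-values, not an error rate of the planned comparison.

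Two further readings are not supported. One is that improvement reflects a new diagnosis: eligibility admits any ACS, neither requires nor excludes earlier coronary disease, and gives no share of first events. The other is that the outcome descriptions contradict Table 1. The text says "Quality of life will be measured 3 months posthospital discharge using the Five-Level EuroQol five-dimension instrument" and "CHD self-management behaviours will be measured 3 months posthospital discharge using the Coronary Artery Disease Self-Management behaviour Scale" without mentioning baseline, but the knowledge outcomes are described in the same way, and the opening of the data collection section refers to Table 1 for the schedule.

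Finally, the choice of contrast can be left to the statistical analysis plan, which is not shown and may settle it. That limits the weight of the point. It does not remove it, because the article itself names within-group change as a target.

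**Conclusion.** The point holds as a matter of analysis wording and precision, not of validity. For secondary outcomes, within-group change is a stated target. For quality of life and self-management it is measured from a score taken during the ACS admission, so it cannot separate the app from recovery and usual care. With 39 per arm, no app effect and an assumed recovery of 0.2 to 0.8 SD of change, a within-arm test would be significant in 23% to 99.8% of trials, against about 5% for the between-group test.

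Using baseline as a covariate would cut the variance to 0.65 to 0.75 of that of a change-score comparison. This assumes a correlation of 0.3 to 0.5, equal variances at the two times, and that the planned model leaves the baseline means free in each arm. If the full analysis plan already adjusts for baseline, this gain is already secured.

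**What to change.** In the Statistical analysis section, drop within-group change as an inferential target for secondary outcomes. Report it descriptively, as mean with SD or confidence interval and no test, noting that it includes recovery from the index event.

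For EQ-5D-5L and self-management, state that the conclusion rests only on the between-group difference at 3 months, estimated with the in-hospital score as a covariate. This agrees with the abstract's commitment to account for baseline differences.

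The cost is a few sentences in the protocol and the analysis plan. The baseline scores are already scheduled, and the sample size does not change. The downside is that the report will carry no within-group p-values.

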### Composition, roles and responsibilities

Trial investigators will monitor enrolment, train study staff and check data quality and confidentiality. Only the investigators on the approved protocol will have access to the final dataset.

### Sample size calculation

Since there is no established minimally important difference in disease knowledge or similar intervention for the CADE-Q SV (Simplified Chinese), the sample size calculation is based on a mean change of 2.3 points (SD 3.6), which has been published in patients with CHD precompleting and postcompleting a comprehensive cardiac education programme.^41^ A total of 78 participants (39 per group) will be required to detect a between-group difference in CADE-Q SV (Simplified Chinese) score of 2.3 points with (α=0.05, 80% power) (calculated from https://sample-size.net/sample-size-means/). Accounting for a 20% dropout rate, 98 patients (49 per group) will be needed.

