### Study groups

#### Control

As determined by the hospitals, participants in the control group will receive usual discharge education from their doctors and other healthcare professionals, such as nurses or pharmacists. This discharge education is usually delivered by a Chinese-speaking health professional or through an English-speaking family member and provides information that summarises discharge, medications and follow-up care, such as cardiac rehabilitation. At the conclusion of the study, control participants will receive a link to download the app.

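### The 2.3-point design difference is a single-group before-after change, so the 80% power is conditional on a net between-group effect that the cited source, as described, does not support

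*Protocol article*

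**What the plan says.** The Sample size calculation section of the protocol article explains its choice by noting that "there is no established minimally important difference in disease knowledge or similar intervention for the CADE-Q SV (Simplified Chinese"). It therefore borrows a before-after figure: "the sample size calculation is based on a mean change of 2.3 points (SD 3.6), which has been published in patients with CHD precompleting" and again after a cardiac education programme. The next sentence gives 78 participants (39 per group) as the number "required to detect a between-group difference in CADE-Q SV (Simplified Chinese) score of 2.3 points" at α=0.05 and 80% power. A 20% dropout allowance brings this to 98 (49 per group).

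The Control section says that "participants in the control group will receive usual discharge education from their doctors and other healthcare professionals", covering discharge, medications and follow-up care such as cardiac rehabilitation. Under Study design, the contrast is the app plus usual care against usual care alone.

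For the analysis, the Statistical analysis section says: "The analysis of variance (ANOVA) will be used to compare the primary outcome and estimate the mean difference and 95% CI". It mentions no baseline term for that ANOVA and adds a linear mixed model over baseline, 1 month and 3 months. The Abstract says that between-group comparisons will account for baseline differences.

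**The concern.** A before-after change in one group and a difference between randomised groups are different quantities. The second equals the intervention arm's gain minus the control arm's gain. The protocol takes a figure it describes as the first kind and uses it as the second, with no deduction and no argument that 2.3 is a plausible net effect. Controls are not untreated, so some gain under usual care is possible.

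The SD raises a related question. The text attaches 3.6 to a change, while the ANOVA named for the primary outcome appears to compare scores. The SDs of change and of score agree only when the baseline-to-follow-up correlation is 0.5.

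At stake is how the result will be read. If the true net difference is well under 2.3, the trial has materially less than 80% power to detect it, and a null result could be taken as evidence that the app does not work.

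**Working it through.** **Inputs from the protocol.** Difference 2.3, SD 3.6, α=0.05, power 80%, 39 per group, 20% dropout (Sample size calculation); 1:1 allocation (Randomisation and blinding). Sidedness is not stated; two-sided reproduces the figure, whereas one-sided gives 31 per group.

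**Inputs assumed.** Control-arm gain and the baseline-to-follow-up correlation r. The document gives neither, so ranges are shown.

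**Step 1: reproduce the plan.** n per group = 2 × (1.960 + 0.842)² × 3.6² / 2.3² = 38.5, rounded up to 39, so 78 in total. Dropout: 78 / 0.8 = 97.5, rounded up to 98. Power at 39 per group for 2.3 points is 80.5% by the normal approximation and 79.5% by the noncentral t. The difference detectable with 80% power is 2.802 × 3.6 × √(2/39) = 2.28 points, so the design has almost no slack.

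**Step 2: deduct a control gain.** Suppose the app-plus-usual-care arm gains 2.3 in total. The net difference is then 2.3 minus the control gain, and its standard error is 3.6 × √(2/39) = 0.815. Two-sided t-test power, unadjusted:

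| Assumed control gain | Net difference | Difference / SE | Power |
|---|---|---|---|
| 0 | 2.3 | 2.82 | 79.5% |
| 0.25 | 2.05 | 2.51 | 70% |
| 0.5 | 1.8 | 2.21 | 59% |
| 1.0 | 1.3 | 1.59 | 35% |

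**Step 3: which SD is 3.6?** If it is the SD of change, and baseline and follow-up scores have equal variance, the score SD is 3.6 / √(2(1−r)). Power of an unadjusted comparison of scores for a true 2.3 points:

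| r | Score SD | Power |
|---|---|---|
| 0.3 | 3.04 | 91% |
| 0.4 | 3.29 | 86% |
| 0.5 | 3.60 | 79.5% |
| 0.6 | 4.02 | 70% |
| 0.7 | 4.65 | 58% |

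The ambiguity can help or hurt, depending on r.

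**Step 4: baseline adjustment.** If 3.6 is the score SD, the adjusted SD is 3.6 × √(1−r²). If it is the change SD, the adjusted SD is 3.6 × √((1+r)/2), which never exceeds 3.6. At r=0.5 both equal 3.6 × √0.75 = 3.12. Power at 39 per group is then about 90% for 2.3, 71% for 1.8 and 44% for 1.3, and the difference detectable with 80% power is 2.28 × √0.75 = 1.98, about 2.0 points.

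**The case against.** The strongest reply is that nothing is miscalculated. The power statement is conditional on a 2.3-point between-group difference, and for that difference it is correct. The protocol also discloses that the source is a before-after figure and says why it was borrowed. All of this stands. But the lack of an established minimally important difference explains borrowing a number; it does not turn a single-group change into a net difference, and no other basis for 2.3 is offered.

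A reader might infer that the design does not deliver its stated power, or that 80% holds only if controls learn nothing. The documents support neither. The second inference needs the premise that the app-plus-usual-care arm gains exactly 2.3 in total. That arm also receives usual care and answers the same questionnaire, so learning from usual care and from repeated testing could occur in both arms and cancel. If the app adds 2.3 points to whatever usual care achieves, power is as stated.

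Nor can it be said that controls will gain. Their education is described as a summary of discharge, medications and follow-up care, while the CADE-Q SV covers disease, risk factors, exercise, nutrition and psychological aspects, so overlap may be limited.

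Finally, baseline adjustment could recover part of any loss. The Abstract points towards it, but neither the ANOVA description nor the sample size calculation uses it, and at r=0.5 it does not restore 80% for a net difference of 1.8.

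**Conclusion.** The concern holds as a mismatch between the design figure and its source, not as an arithmetic error. N=98 is correctly derived for a net 2.3 points at SD 3.6, but the source as described measures something else, and no allowance for control gain is stated. The possible loss can only be given as a range: if the app arm gains 2.3 in total, unadjusted power falls from 79.5% to 59% with a control gain of 0.5 and to 35% with a gain of 1.0. The SD ambiguity is secondary and has no fixed direction: unadjusted power for 2.3 is 86% at r=0.4 and 58% at r=0.7 if 3.6 is the SD of change. All of these figures assume 39 evaluable per group and a two-sided 5% test; the control gains and correlations are assumptions.

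**What to change.** Keep N=98 and revise the sample size paragraph to:

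- say that 2.3 is a single-group before-after figure used as the target, and that 80% power is conditional on a net between-group difference of that size;
- give unadjusted power at 39 per group for smaller net differences (59% for 1.8, 35% for 1.3, at SD 3.6);
- say whether 3.6 is the SD of change or of score;
- base the power statement on a baseline-adjusted comparison with the assumed correlation stated (at r=0.5, about 90%, 71% and 44% for 2.3, 1.8 and 1.3).

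In the Statistical analysis section, make that baseline-adjusted comparison the primary one. Baseline knowledge is already collected according to Table 1.

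The cost is one rewritten paragraph and a matching edit to the analysis section, with no extra patients or assessments. The downside is that power will be shown as lower for smaller net differences.
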